### Study aims

The 5 year study was developed in partnership with Education Queensland’s Transition Support Service (TSS) in response to increased suicide risk identified in transitioning students. It was funded by the National Health and Medical Research Council from December 2014. The study will investigate the impact of an enhanced multicomponent mentoring intervention to increase levels of psychosocial resilience among the 515 remote Aboriginal and Torres Strait Islander students from Cape York and Palm Island, who are compelled to relocate to boarding schools across Queensland when there is no secondary schooling provision in their home communities. We aim to test the null hypothesis that students’ resilience is not positively influenced by the multicomponent mentoring suicide prevention intervention. The objectives of this study are to:Enhance the existing TSS case management approach by supporting a multi-component mentoring intervention for staff and assessing its impact;Identify and apply valid and reliable quantitative outcome measures to assess the impact of the enhanced resilience-based service delivery model for Aboriginal and Torres Strait Islander students using an interrupted time series design;Apply cost analysis methods to calculate the economic costs of the intervention; andApply grounded theory methods to theorise and explain the process by which psychosocial resilience was enhanced to protect against suicide for Aboriginal and Torres Strait Islander students, including the contextual factors.

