Taking account of an expected drop-out rate of senior students who complete school; and the high likelihood of tracing students due to the close linkages between TSS staff with students and their families, we expect a follow up rate of 80 % at mid-point (*n* = 412) and 80 % at post-intervention (*n* = 330). These sample size calculations are based on population measures and study design. The primary outcome measures will be resilience (measured using the CYRM), and school participation (measured through routine data and including a composite indicator comprising uptake of placements at boarding schools at start of grade 7; uptake of the first scheduled flights to boarding schools each term; and a reduction in the rate of suspension for students who re-engage for issues that relate to not staying enrolled). Based on previously conducted studies using ANOVA for analysis, we assumed a 10 % effect size [53]. This is very conservative. We assumed a standard deviation of (0.3). Sample size calculations for an alpha level of 5 %, with power 80 %, *n* = 68 students per group, which will sufficiently enable statistical testing of the hypothesised differences. Since we had planned to sample *n* = 172 mentored students per group, about three times the sample size required, we are confident that our sample will be adequate for additional group-specific stratified analyses. The identified results of the routinely collected and screening survey data will be fed back to TSS staff to tailor the development of mentees’ aspirational plans. Following the baseline screening survey, the same instrument will be implemented at the end of the academic year and upon completion of the following two academic years.

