A fixed cohort approach is planned [54] with the above-mentioned outcome measures for the 172 mentored students in group 1 compared pre- and post-intervention and to measures for the 172 students in groups 2 and 3. Separate statistical analyses will be undertaken for each outcome for each group using the statistical software program, STATA. The biennial proportion of students with each outcome of interest will be considered as a continuous measure for the analyses. Evaluation of the intervention effect in an interrupted time series design involves fitting a disjointed, segmented, linear regression model for the proportion of individuals with the outcome of interest over time, separately for each group. The models will include separate intercepts and slopes for both pre- and post-intervention (the two “segments”) and a term for site. For the intercepts, an intervention effect will be identified by a change or ‘jump’, in the primary outcome from pre- to post-intervention. For the slopes, an intervention effect will identified by a change in trend from pre- to post-intervention [55]. Examination of the magnitude of these coefficients will determine whether they are statistically significant.

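### Two primary outcomes, three separately analysed groups and two effect coefficients per model, with no deciding test and a significance rule based on coefficient magnitude

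*Protocol article*

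**What the plan says.** Study aims gives one hypothesis, directional and about resilience alone: "We aim to test the null hypothesis that students’ resilience is not positively influenced by the multicomponent mentoring suicide prevention intervention".

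Objective 2, sample-size paragraph, names two primary outcomes: "The primary outcome measures will be resilience (measured using the CYRM), and school participation", the latter a composite from routine data. The only error rate in the article is in the same paragraph: "Sample size calculations for an alpha level of 5 %, with power 80" per cent, for a single comparison.

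Objective 2 also sets out three randomised clusters starting in 2016, 2017 and 2018, so that each group serves as a comparison for itself and for the others.

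The analysis paragraph then states: "Separate statistical analyses will be undertaken for each outcome for each group". Each analysis is a segmented linear regression, fitted separately by group, with its own intercept and slope before and after the intervention. A change in intercept identifies an intervention effect; so does a change in slope. The paragraph closes with the decision rule: "Examination of the magnitude of these coefficients will determine whether they are statistically significant".

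**The concern.** The plan positively fixes several separate places where an effect may be found, and does not say which one answers the hypothesis. A reader of the results could not tell whether a slope change in one group on school participation, with nothing on resilience, counts as success. Nor could they tell what to conclude if the three groups disagree.

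The closing sentence adds an error of its own. A coefficient's size does not determine its statistical significance; its size relative to its standard error does. A large coefficient from a few time points may be compatible with no effect, and a small one estimated precisely may not be.

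The Discussion says the study should show whether the programme works and help governments decide what to fund on a recurrent basis. That use needs a test with a known error rate.

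**Working it through.** **The plan's own figure.** The article gives no overall error rate to reproduce, only alpha 5% for one comparison. The sample size attached to it, 68 per group, does not follow from the stated 10% effect (read as 0.10) and SD 0.3:
- Two-group comparison, two-sided 5%, 80% power: 2 × (0.3 × 2.8016 / 0.10)² = 141.3, so 142 per group.
- One-sample form: (0.3 × 2.8016 / 0.10)² = 70.6, so 71.

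That is a separate matter, and nothing below depends on it.

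**Inputs from the text**
- Primary outcomes: 2 (sample-size paragraph).
- Groups analysed separately: 3 (design and analysis paragraphs).
- Coefficients per model that identify an effect: 2, level and slope (analysis paragraph).

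**Inputs assumed**
- Each coefficient is tested at 5%. The analysis paragraph sets no level; 5% is borrowed from the sample-size sentence.
- Any one significant coefficient counts as an effect. The text states no other rule, but does not state this one either.
- Sidedness is not given. The hypothesis is directional, so two forms are shown.

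**Count.** All routes: 2 × 3 × 2 = 12. Routes bearing on the stated hypothesis (resilience only): 1 × 3 × 2 = 6.

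**Chance of at least one false positive among k independent tests at level a: 1 − (1 − a)^k**

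| Reading | Calculation | Result |
|---|---|---|
| Resilience only, beneficial direction, 2.5% each | 1 − 0.975^6 | 14.1% |
| Resilience only, 5% each | 1 − 0.95^6 | 26.5% |
| All routes, beneficial direction, 2.5% each | 1 − 0.975^12 | 26.2% |
| All routes, 5% each | 1 − 0.95^12 | 46.0% |

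The second row holds whether the 5% is two-sided or spent wholly on the beneficial side.

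**Correlation.** Level and slope from one model are correlated, and the groups share calendar years and a support service. Simulated with a common correlation between all coefficients, 5% two-sided each:

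| Correlation | 6 routes | 12 routes |
|---|---|---|
| 0.3 | 24.1% | 39.5% |
| 0.5 | 20.7% | 32.1% |
| 0.7 | 16.4% | 23.3% |
| 0.9 | 10.8% | 13.4% |

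**Estimability.** Student surveys begin at the start of the 2016 school year, the year in which group 1 starts. Group 1 thus appears to have one resilience measurement before the intervention, and a slope cannot be estimated from one point. Removing its two resilience coefficients leaves:
- 4 resilience routes: 1 − 0.975^4 = 9.6% (beneficial only) to 1 − 0.95^4 = 18.5%.
- 10 routes overall: 1 − 0.95^10 = 40.1%.

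**Other decision rules**
- Both primary outcomes must succeed, each by any of its six routes: 0.265² = 7.0% if independent.
- All three groups must show a resilience effect by either coefficient: (1 − 0.95²)³ = 0.0975³ = 0.09% if independent.

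The rate therefore runs from well below 5% to several times 5%, depending on a rule that the article does not give.

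**The case against.** The strongest reply is that the any-one-of-twelve rule is the reader's inference. The analysis paragraph explains how level and slope changes are interpreted in a segmented regression. It does not say that one significant coefficient in one group rejects the hypothesis. The design paragraph has the groups serve as comparisons for each other, and the analysis paragraph compares group 1 with groups 2 and 3, so reading the groups together is natural. This stands as a limit on the numbers, but the article fixes no joint rule either, and it specifies separate fits.

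A reader might infer that a stated 5% error rate is breached and that the true rate is 46%. The document does not support that. The 5% appears only in the sample-size sentence, and no overall rate is claimed. The stated hypothesis covers at most six routes, and 46% needs all twelve to be independent. Taken literally, a magnitude rule has no 5% level at all.

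It can also be said that sharing of alpha belongs in a statistical analysis plan, which is not shown. Silence on adjustment alone would indeed be no finding. But the article does fix two primary outcomes against a one-outcome hypothesis, separate models, two identifying coefficients and a significance rule.

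Finally, the magnitude sentence may be loose wording for ordinary coefficient tests. That is plausible, but it is the only decision rule printed and it is incorrect.

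**Conclusion.** The point holds as a defect in the decision rule. The article gives two primary outcomes against a resilience-only hypothesis and several coefficients that may each identify an effect, and it does not say which decides.

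If each is tested at 5% and any one suffices, the false-positive chance on the stated hypothesis is about 14% to 26.5% with independent coefficients. It is at most 46% over all twelve routes. Correlation, and group 1's doubtful resilience coefficients, bring these down. They show what the text permits; they are not the trial's established error rate.

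The error in the magnitude sentence rests on none of these assumptions and needs correction in any case.

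**What to change.** - **Confirmatory test.** Name one intervention coefficient for the CYRM (state in advance whether level or slope), from one model combining the three staggered groups, tested at two-sided 5%. This uses the between-group comparison the design already intends and matches the stated hypothesis.
- **Second primary outcome.** Test school participation only if the CYRM test succeeds (fixed sequence), or test both by Holm.
- **Supportive results.** Report group-specific results and the remaining level or slope coefficients with confidence intervals, without a claim of effect from any one of them.
- **Significance sentence.** Replace the magnitude rule with estimate, 95% confidence interval and p-value, using standard errors that allow for clustering by school.

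Cost: the text change is short, but it does alter the primary model, since the group-by-group regressions become supportive. School participation is tested only after the CYRM, or under Holm at a stricter first step of 2.5% (5% / 2). No extra data collection is needed.

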**Fig. 2 Fig2:**
[figure not shown]
Research deliverables

Selection criteria for the inclusion of schools will be collaboratively negotiated with TSS. The criteria will likely include: 1) having an enrolment of at least 10 TSS-supported students at the school and 2) being representative of the five TSS regions. We will also collect data for students from routinely available education indicators such as school attendance, retention. We will repeat the process with the second and third clusters of schools from 2017 to 2018.

We will assess the impact of the suicide prevention intervention on students’ resilience using: 1) routinely collected school outcomes data; and 2) screening survey data for the aggregated student cohort. Data routinely collected by Education Queensland (school attendance, retention and post-school destination) reflects suicide protective factors. Survey measures will be refined by the project steering group, but we anticipate a tailored instrument incorporating: resilience (individual capacities/ resources, relationships with primary caregivers and contextual factors that facilitate a sense of belonging), accompanied by the Kessler 5 psychological distress scale and suicidal risk factors, supplemented by questions assessing frequency of happy and angry feelings. Resilience will be measured using the Child and Youth Resilience Measure (CYRM) which has been validated internationally [53]. The suicide risk assessment questions are standard screening questions which were identified by a local Indigenous medical practitioner and CI as most relevant for Cape York students. The screening instrument will also include questions about services of which students are aware and access and transition strategies that they perceive to work. Using agreed measures, an online student screening survey will be integrated into TSS processes for student placements into boarding schools and administered using iPads to students in each cluster at the start of the 2016, 2017 and 2018 academic years.

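### The primary CYRM resilience scale is analysed only as a group-level proportion with no stated cut-off, although the study appears to be sized on a difference in means

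*Protocol article*

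**What the plan says.** All of this is in the protocol article, Methods/Design, Objective 2, except the hypothesis, which is in Study aims.

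- **Hypothesis.** It concerns resilience: "We aim to test the null hypothesis that students’ resilience is not positively influenced by the multicomponent mentoring suicide prevention intervention".
- **Primary outcomes.** "The primary outcome measures will be resilience (measured using the CYRM), and school participation". The second comes from routine data and includes a composite indicator.
- **Instrument.** "Resilience will be measured using the Child and Youth Resilience Measure (CYRM) which has been validated internationally". No threshold separating resilient from non-resilient students is given.
- **Sizing.** "Based on previously conducted studies using ANOVA for analysis, we assumed a 10 % effect size"; then "We assumed a standard deviation of (0.3"); then "Sample size calculations for an alpha level of 5 %, with power 80" %, giving "68 students per group, which will sufficiently enable statistical testing of the hypothesised differences". The plan is for 172 per group in three groups.
- **Analysis.** "The biennial proportion of students with each outcome of interest will be considered as a continuous measure for the analyses". A segmented linear regression of that proportion over time is fitted separately for each group, with separate pre- and post-intervention intercepts and slopes and a site term. The effect on the primary outcome is read from the jump and the change in slope.

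No other quantitative analysis of resilience is described.

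**The concern.** The CYRM is a scale and gives each student a score. A proportion of students with the outcome exists for it only after the score has been cut at a threshold, and the article names none. As written, the rule for the outcome in the main hypothesis cannot be applied without a further choice, and the result would depend on that choice.

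Two losses follow. Cutting a score discards information, so more students are needed for the same power. Collapsing students to one proportion per group and wave also reduces the data entering the regression from hundreds of scores to a handful of points. The quantity tested changes too: it becomes a shift in the share above a threshold, whereas an effect with an SD under ANOVA points to a difference in mean score.

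**Working it through.** **Inputs.** From Objective 2: effect 10% (taken as 0.1), SD 0.3, alpha 5%, power 80%, 172 per group. Expected follow-up is 412 at mid-point (412/3 ≈ 137 per group) and 330 post-intervention (330/3 = 110). Assumed here: two-sided test, normal score, independent students, cut-offs with 20% to 80% of students above at baseline.

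**Step 1: the plan's own figure of 68.** Two independent means:
n = 2(1.960 + 0.842)² × (0.3/0.1)² = 2 × 7.849 × 9 = 141.3, so 142 per group (112 one-sided). The paired form, with 0.3 as the SD of the change, gives 7.849 × 9 = 70.6, so 71. With 0.3 as the SD at each occasion, the paired form gives 68 only if a pre-post correlation of about 0.52 is assumed, which is not stated. A three-group ANOVA gives 132 per group if one mean differs by 0.1. So 68 does not reproduce from the stated inputs. That is a separate problem; 142 is the reference below.

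**Step 2: the same effect after cutting the score.** The shift is 0.1/0.3 = 0.333 SD. If a share p₁ is above the cut without the intervention, the share with it is p₂ = Φ(Φ⁻¹(p₁) + 0.333). With p̄ the mean of p₁ and p₂:

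n = [1.960√(2p̄(1−p̄)) + 0.842√(p₁(1−p₁) + p₂(1−p₂))]² / (p₂−p₁)²

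Median split: p₂ = Φ(0.333) = 0.631 and p₂ − p₁ = 0.131, so n = (1.374 + 0.585)²/0.131² ≈ 226.

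| Analysis | n per group for 80% | Power at 172 | at 137 | at 110 |
|---|---|---|---|---|
| Score | 142 | 87.1% | 78.8% | 69.6% |
| Proportion, 50% vs 63.1% | 226 | 68.7% | 58.8% | 49.7% |
| Proportion, 20% vs 30.6% | 265 | 61.6% | 52.1% | 43.7% |
| Proportion, 80% vs 88.0% | 329 | 52.5% | 43.8% | 36.5% |

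The ratio for the median split is 226/142 = 1.59. The true optimum, a cut midway between the two means (43.4% vs 56.6%), gives 223 and 69.1% power at 172, so the median split is within rounding of the best case.

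**Step 3: degrees of freedom.** Objective 2 describes a baseline survey, one at the end of that academic year, and one at the end of each of the next two years: four waves. With one proportion per group per wave, two intercepts and two slopes are four parameters.

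- Two waves before and two after: 4 − 4 = 0 residual degrees of freedom, so no standard error.
- One wave before: the pre-intervention slope cannot be estimated; three parameters remain, with 4 − 3 = 1 degree of freedom.

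Objective 2 also mentions surveys at the start of 2016, 2017 and 2018. If these are extra rounds for every group, there are six points and, with two before, 6 − 4 = 2 degrees of freedom. The site term is not counted.

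**The case against.** The strongest reply is that planning on means is an inference. The article never says that 0.3 is the SD of the CYRM score, and the 10% has no stated scale. An SD of 0.3 is also √(0.1 × 0.9), that of a binary outcome at 10%. This stands as a caveat. The ANOVA wording favours means, and reading 10% as a 10-point difference in proportions did not give 68 at the baselines tried. On either reading the CYRM still has no cut-off.

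Proportions over time are ordinary in interrupted time series and suit parts of school participation, such as uptake of places and flights. This also stands: the point is confined to the CYRM and other scale scores such as the Kessler 5.

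A separate analysis plan might supply a cut-off. That would make the analysis runnable but would not recover the lost information. The site term suggests that proportions may be formed by site, which would ease the shortage of degrees of freedom but not the loss from cutting.

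Four stronger readings are tempting and not supported:

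- **That 172 per group is too few for any 10-point difference.** 10% vs 20% needs 199 and 50% vs 60% needs 388, but 5% vs 15% or 85% vs 95% needs only 141.
- **That site proportions rest on about 10 students.** Ten is a likely minimum TSS enrolment for including a school, still to be negotiated, and site is undefined.
- **That the regression is unweighted.** The article does not mention weights.
- **That pre-post information is ignored altogether.** A fixed cohort is planned and compared pre- and post-intervention. Only the narrower statement holds: the regression described has no student-level baseline term.

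**Conclusion.** The concern holds for the CYRM and other scale scores. The only analysis described for the outcome in the main hypothesis needs an unstated threshold, and it tests a different quantity from the difference in means that the sizing appears to use. With a difference of 0.1, SD 0.3, a normal score, a two-sided 5% test and no clustering, moving from score to proportion raises the requirement from 142 to about 226 per group at best. Power at 172 falls from 87% to about 69%, and to about 53% at the worst cut-off considered. Even the best cut-off misses the planned 80% with every student followed. If proportions are formed per group and wave over four waves, the segmented model has no residual degrees of freedom.

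The mismatch is in the text. The size of the loss depends on the assumed cut-off, on normality, and on taking 0.1 and 0.3 as the CYRM's difference and SD. Clustering is left out of both sides of the comparison, so the power figures are not forecasts for the trial. A reader might infer that every proportion in the plan is wrong; the documents do not support that.

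**What to change.** For the CYRM, and other scale scores such as the Kessler 5, replace the proportion model by a linear mixed model of each student's repeated scores, with:

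- a student random effect (or the baseline score as a covariate);
- a random effect for the randomised school or group of de-enrolled students;
- calendar-time terms;
- an intervention term switched on at each cluster's staggered start (2016, 2017 or 2018), with a change in slope if the number of waves allows it.

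Report the mean difference with its 95% confidence interval. Calendar time and the randomised unit should not be dropped: a model with baseline score alone could confound the intervention with time and understate standard errors.

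Restate the sample size and power for that model, saying which outcome the effect and SD belong to. Keep proportions for outcomes that are naturally binary or rates, and for graphs.

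Cost: the survey is to be given to individual students, so no new data are needed. The analysis takes somewhat more work, the sample size has to be redone, and the restated requirement will probably look less favourable than 68 per group. The change should be made before outcome data are analysed.

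### The CYRM resilience score is sized as a continuous outcome but, read literally, would be tested as a proportion of students

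*Protocol article*

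**What the plan says.** All the relevant text is in Methods/Design, Objective 2.

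- **Outcomes.** "The primary outcome measures will be resilience (measured using the CYRM), and school participation". School participation is a composite of placement uptake, flight uptake and suspensions.
- **Sample size.** "Based on previously conducted studies using ANOVA for analysis, we assumed a 10 % effect size". The SD is taken as 0.3. The result is given as "Sample size calculations for an alpha level of 5 %, with power 80 %, *n* = 68 students per group", against 172 planned per group. The effect size carries the same reference number (53) as the CYRM validation.
- **Analysis.** "Separate statistical analyses will be undertaken for each outcome for each group", using the outcome measures already listed. "The biennial proportion of students with each outcome of interest will be considered as a continuous measure for the analyses". The model is described as "fitting a disjointed, segmented, linear regression model for the proportion of individuals with the outcome of interest over time", fitted per group, with separate intercepts and slopes before and after the intervention and a term for site.

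The article describes no model for a score, and it does not say what it means for a student to have the resilience outcome.

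**The concern.** The CYRM measures resilience as a matter of degree, and the stated null hypothesis is about resilience. An effect size with an SD, drawn from ANOVA studies, belongs to a comparison of means. A proportion of students with the outcome belongs to a yes/no variable. The two paragraphs fit together for the CYRM only if the score is cut in two.

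Two things are at stake. First, the quantity tested would differ from the quantity that was sized, so the stated power would not apply to the test. Second, splitting a graded score usually discards information: movement on either side of the cut is ignored, and the result depends on where the cut is placed. The same survey data would support an analysis that avoids both problems.

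**Working it through.** **1. Inputs.** From the sample-size paragraph: difference 0.10 (the 10% effect, read as absolute), SD 0.3, alpha 5%, power 80%, stated n 68 per group, planned n 172 per group. So d = 0.10/0.3 = 0.333. Assumed here, because the article does not give them: two-sided test, normal scores, independent students, and a cut leaving 50% or 20% of students in one category.

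**2. The plan's own figure.** For two means, n = 2(1.96 + 0.842)² × 0.3²/0.1² = 2 × 7.85 × 9 ≈ 142 per group two-sided (112 one-sided), not 68. The nearest variant tried is a one-sample or paired calculation, 7.85 × 9 ≈ 71, for which 68 gives 78.5% power. The origin of 68 is a separate matter. Here it means only that d = 0.333 is a reading of the inputs, not a confirmed design value.

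**3. Power on the mean, 172 per group.** Φ(d√(n/2) − 1.96) = Φ(0.333 × 9.27 − 1.96) = Φ(1.13) = 87.1%.

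**4. Power on a proportion, 172 per group.** The same shift moves the share beyond the cut from p0 to p1. Power = Φ{[|p1 − p0|√n − 1.96√(2p̄(1 − p̄))]/√(p0(1 − p0) + p1(1 − p1))}, where p̄ is the average of p0 and p1.

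| Scale tested | p0 → p1 | Power | Loss (points) |
|---|---|---|---|
| Mean score | – | 87.1% | – |
| Median cut | 0.500 → 0.631 | 68.7% | 18 |
| 20% above the cut, share rises | 0.200 → 0.306 | 61.6% | 26 |
| 20% below the cut, share falls | 0.200 → 0.120 | 52.5% | 35 |

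For 80% power, the n per group rises from 142 to 226 (median cut), or to 265 and 329 (20% cut, by direction).

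**5. Efficiency under normality.** φ(c)²/[p(1 − p)], where c is the cut in SD units, is 0.64 at the median, 0.49 at a 20% cut and 0.34 at a 10% cut.

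**6. How far the figures move.**

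| Setting | Loss in power (points) |
|---|---|
| 68 per group, cuts 50% to 20% | 16 to 25 |
| 110 per group (330/3), same cuts | 20 to 33 |
| 137 per group (412/3), same cuts | 20 to 35 |
| 172 v 344, same cuts | 14 to 28 |
| 172 per group, 10% cut | 38 to 50 |
| 172 per group, d = 0.48, cuts 50% to 20% | 5 to 19 |

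The last row uses the effect that 68 per group detects with 80% power: 2.80 × √(2/68) = 0.48.

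The shape of the distribution matters too. Median-cut efficiency is 4f(0)²σ², where f(0) is the density at the median. It is 0.64 for a normal score, 4 × (1/16) × π²/3 = 0.82 for a logistic score, and 4 × 0.25 × 2 = 2 for a double-exponential score, where the split would lose nothing.

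**The case against.** The strongest reply is that nowhere does the article say the CYRM will be cut. The proportion wording reads like standard interrupted-time-series text and suits the school indicators. Survey measures are still to be refined by the steering group, and a scoring rule could sit in a fuller protocol or analysis plan. The sample-size inputs are not tied to the CYRM by name, and 0.3 is also √(0.1 × 0.9), the SD of a yes/no outcome at 10%.

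Part of this stands. Dichotomisation is an inference, and a missing cut-point is not itself the fault. But the analysis paragraph does not leave the scale open: it sets a proportion for each outcome, and the CYRM is one of them. A later plan that analyses the score would contradict it, and one that follows it would have to cut the score. The binary reading of 0.3 does not fit the ANOVA reference or the citation shared with the CYRM. It also does not give 68: going from 10% to 20% needs 199 per group.

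It is also fair to say that the power figures belong to a simple two-group test. The planned model uses aggregate proportions within each group, and its power also depends on the number of time points, clustering and repeated measures on the same students. That stands in full.

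**Conclusion.** The mismatch holds. The sample-size paragraph treats resilience as continuous, and the analysis paragraph, read literally, treats it as a proportion. The stated method is weaker than an obvious alternative on the same data. Under the illustrative assumptions, power falls from about 87% to about 69% at a median cut and to 53% to 62% at a 20% cut.

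A reader might infer more than the document supports:

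- **That at least 36% of the information is lost.** This is 1 − 2/π, a bound for normal scores only. A logistic score loses about 18% at the median, and the article does not give the CYRM distribution.
- **That the trial loses 18 to 35 points of power.** This needs d = 0.333, 172 per group, cuts between 50% and 20%, and a test that is not the planned one.
- **That the article announces a split of the CYRM, or that this is the only primary test.** The first is inferred from the wording about each outcome. On the second, school participation is also primary, and routine school data also feed the assessment of resilience.

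**What to change.** In the analysis paragraph of Objective 2:

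- State that the CYRM score is analysed as a continuous outcome, either as the student-level score or as the mean score in the segmented model, allowing for repeated measures and site.
- Keep proportion models for outcomes that are truly yes/no, such as the components of school participation.
- Treat any share of students above a CYRM cut as descriptive.
- In the sample-size paragraph, say which outcome the inputs refer to and give power on the scale that is tested.

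If a proportion is nevertheless wanted for the CYRM, the cut should be fixed in advance and the sample size redone for that proportion. The cost is a change of model for one primary outcome and a restated power figure. Data collection does not change.
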